#### Concealment mechanism {16b}

Data from each trial will be labeled with non-descriptive identifiers. The participant will not be told the modification made to each socket but will be allowed to see and touch the socket, as this is inevitable when using the prosthesis.

#### Implementation {16c}

The allocation sequence will be generated by the study statistician who is not involved in the data collection. All participants in either study phase will be enrolled by the study PI and will eventually be exposed to all interventions of the study phase in a randomized sequential order.

### Assignment of interventions: blinding

#### Who will be blinded {17a}

The research technician and engineer will be blinded to the socket modification when processing radiographic data from each trial, which will be labeled with non-descriptive identifiers. Effective blinding of trial participants, care providers, and data collection personnel will not be possible as the appearance of the prosthesis cannot be altered without affecting relevant characteristics (such as fit or weight).

#### Procedure for unblinding if needed {17b}

Upon conclusion of the analysis, participants and study personnel will be provided with the unblinding key (i.e., a list with the individual intervention sequence).

### Data collection and management

#### Plans for assessment and collection of outcomes {18a}

##### PROMs

Participants will be asked to rate their overall perception of the (1) comfort and (2) function of each socket relative to their current socket on a scale ranging from − (a very great deal worse) to 0 (about the same) to 7 (a very great deal better) using a global rating of change scale [38] (GRC). The GRC scale was selected over other questionnaires because, intuitively, it makes sense that a patient’s perception of comfort and function gives a more accurate assessment if a true change has occurred rather than a prognostic rating [39]. The Prosthetic Limb Users Survey of Mobility (PLUS-M) 12-item short form will be collected after wearing of each socket to provide a secondary measure of perceived mobility. In addition, participants will be completing the OPUS device satisfaction survey to establish baseline satisfaction with their current device and the Amputee Mobility Predicter with prosthesis (AmpPro), attached, to assess their mobility level. All of these data will be collected via tablet using the REDCap system, a secure, web-based application designed to optimize data collection. The REDCap system is currently in place and used to collect data for ongoing research studies in the Biodynamics Lab.

##### CT scans

We will acquire a CT scan of the residual femur from each participant. The scan will include a series of 0.625-mm slices from the proximal to the distal end of the residual femur.

##### Hip strength and ROM

Hip abductor and flexor strength will be measured with a hand-held dynamometer (HHD) (Lafayette Instrument, Lafayette, IN) using previously established protocols [40] modified for amputees. Hip abductor strength will be measured with the participant side-lying on an examination table with the test hip facing up (Fig. 9). The non-test leg is bent at the hip and knee for stability. The test hip is in neutral flexion/extension and rotation. The moment arm is recorded as the distance in centimeters between the greater trochanter and the HHD. A non-elastic strap is used to secure the dynamometer against the leg and provide resistance to hip abduction. The strap is wrapped around the leg and underneath the table. The participant is asked to push up against the HHD as hard as possible for 4 s (substantial reliability; ICC .95) [41]. This procedure will be repeated to test hip flexor strength with the participant supine on the exam table and arms across the chest. Hip range of motion will be measured with a standard long-arm goniometer during active (moved by the participant) and passive (assisted by the tester) movements with the participant standing upright using crutches to balance.

**Fig. 9 Fig9:**
[figure not shown]
The hip abductor test

##### Dynamic biplane radiography

Participants will then walk at their self-selected pace which will be held constant by the treadmill while wearing each of the 9 socket designs. We selected walking because it is the most common lower body functional activity, and comfort and function during walking have a major impact on amputee quality of life. After donning the socket, the participant will be allowed time to acclimate to each socket by walking on the treadmill for up to 5 min. After acclimation, we will collect a total of three trials for each of the 9 sockets. We will collect synchronized biplane radiographs for 1 s at 100 images per second to image the residual femur and skin motion within the socket during the late swing through push-off phase of gait. Images will be collected with 1-ms exposures in all cases to minimize motion blur and radiation exposure. Three-dimensional (3D) skin motion within the socket will be determined by tracking the motion of 40 to 50 small metal beads (1 to 2 mm diameter) that will be secured to the skin of the residual limb in a grid pattern before donning the socket (Fig. 2A). Beads will be secured using Quick Grip glue, a type of contact cement that does not permanently bond to the skin like Super Glue but is strong enough to hold the bead to the skin without moving. Residual femur motion will be determined with sub-millimeter accuracy using a validated volumetric model-based tracking process that matches subject-specific bone models obtained from CT to the biplane radiographs [42–44] (Fig. 10).

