### Outcomes {12}

Outcomes for each participant will be averaged across three trials for each of the interventions, to analyze the change from baseline with different socket designs.

Many of the assessment methods are identical or equivalent to clinical assessment instruments that are associated with high validity and low risk for the target population. The effective radiation dose due to dynamic biplane radiography is estimated to be 2.0 mSv or less for the 27 trials collected for each participant. For comparison, the average effective dose associated with a knee CT scan from our previous studies was 1.4 mSv, and in the USA, we receive about 3.0 mSv of exposure from natural background radiation every year [37].

The following is the primary outcome variable:
*Socket comfort*

The following are the secondary outcome variables:
*Hip range of motion (ROM)**Three-dimensional (3D) skin motion within the socket**Residual femur position within each socket**In-socket pressure**Plantar pressure**Ground reaction forces during gait**Overall body motion (e.g., trunk lean, hip flexion/extension) during gait*

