#### Participant timeline {13}

Participants in the first stage (aims 1 and 2) of the study, upon eligibility screening and completing the consent process, will be fitted for a check socket. After 4 weeks, during which time 8 derivatives of the socket will be produced, participants will complete testing with each of those socket variants over one or two lab visits. The participant timeline for the second stage (aim 3) includes clinical testing of one socket variant and spans a larger period (Fig. 8).

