### Assignment of interventions: allocation

#### Sequence generation {16a}

The order of the modified sockets worn by each participant will be randomized using computer-generated random numbers.

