## Statistical methods

### Statistical methods for primary and secondary outcomes {20a}

#### Aim 1

The effects of in-socket mechanics, such as residual bone motion, peak skin strain, and pressure distribution on both physical function and patient-reported outcomes will be assessed using a generalized linear model (GLM). We will examine the effect(s) of each in-socket mechanical parameter on outcomes by utilizing the type III sum of squares tables. If our sample size drops below 30, we will develop separate models for each of the parameters of interest and outcome. Finally, we will create a unified model, containing the statistically significant parameter coefficients, which will allow us to predict physical function and patient response based on the changes to the included parameter estimates.

#### Aim 2

We will use partial correlation to examine the association between residual femur motion, skin strain, pressure, and readily available clinical measurements, while adjusting for potential confounders such as residual femur length (derived from CT data), overall residual limb length (measured from ischial tuber to distal end of the limb by caliper), contraction potential (tape measured as the difference of circumferential volumes during thigh muscle contraction and relaxation), and soft-tissue coverage (measured as a ratio between thigh and femur diameter). Partial correlation is a measure of the strength and direction of a linear relationship between two continuous variables whilst controlling for the effect of one or more other continuous variables (also known as “covariates” or “control” variables). Although partial correlation does not make the distinction between independent and dependent variables, the two variables are often considered in such a manner (i.e., you have one continuous dependent variable and one continuous independent variable, as well as one or more continuous control variables). If data is not approximately normal, we will use log transformations. Moderate-to-strong, significant correlations between research-grade and clinical data will be retained for empirical testing in aim 3.

#### Aim 3

Statistical analysis for aim 3 will involve two parts. First, the predictive model developed in aims 1 and 2 will be tested using data from 15 new participants (i.e., data not used to create the model). Second, we will compare the quantitative socket design to the current standard of care, in terms of patient outcomes and cost.

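### Aims 1 and 2: random socket order does not protect associations between measured variables, so if socket-level data are analysed, test position and visit should be covariates

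*Protocol article*

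**What the plan says.** **Exposure.** Under Dynamic biplane radiography, "we will collect a total of three trials for each of the 9 sockets", and before those trials "the participant will be allowed time to acclimate to each socket by walking on the treadmill for up to 5 min". Participant timeline {13} adds that "participants will complete testing with each of those socket variants over one or two lab visits".

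**Order.** Sequence generation {16a}: "The order of the modified sockets worn by each participant will be randomized using computer-generated random numbers".

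**Data.** Item {12}, on outcomes, sets the level at which results are summarised: "Outcomes for each participant will be averaged across three trials for each of the interventions, to analyze the change from baseline with different socket designs". The PROMs section has comfort and function rated for each socket against the current one. Trial design {8} describes a single-group crossover.

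**Analysis.** Statistical methods {20a} assesses aim 1 with a generalized linear model of function and patient-reported outcomes on bone motion, skin strain and pressure: "We will examine the effect(s) of each in-socket mechanical parameter on outcomes by utilizing the type III sum of squares tables". Aim 2 uses partial correlation "while adjusting for potential confounders such as residual femur length (derived from CT data), overall residual limb length", and the list continues with contraction potential and soft-tissue coverage. Neither aim names a term for test position or visit. The significant aim 1 coefficients form a unified predictive model, and significant aim 2 correlations of at least moderate strength go forward to aim 3.

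**The concern.** Random order makes test position independent of socket design, on average. It does not make position independent of the measurements taken at that position. In aim 1 the exposure is measured mechanics and the outcome is a rating. In aim 2 both variables are measured. Neither side of either association is what was randomised.

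Tiredness, skin soreness, change in limb volume, or re-application of beads and pressure pads at a second visit could plausibly move both variables. Position or visit would then be a confounder within each participant. Femur length, limb length, contraction potential and soft-tissue coverage are constant within a participant and cannot remove it.

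The plan selects on significance. A false association would therefore enter the predictive model, or the set of clinical predictors, on which the aim 3 socket design rests.

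**Working it through.** **1. The plan's own figure.** Sample size {14} gives n = 30, f² = 0.45, three mechanics parameters, α = .05 and 80% power. For the overall F test take u = 3, v = N − u − 1 and λ = f²N.
- N = 28 gives 79.2% power and N = 29 gives 81.0%, so the required N is 29.
- N = 30 gives 82.7%.

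The stated figure reproduces and is not disputed. It treats 30 observations as independent, so it is silent on whether socket-level rows will be analysed.

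**2. Inputs to the bias check.**
- From the article: 30 participants, 9 sockets, random order, one or two visits.
- Assumed: the drift. D is the shift from first to last socket in units of the within-participant noise SD, linear over position and equal in both variables.
- Assumed: a socket effect on mechanics with SD 0.5 (variance 0.25), and no true link between mechanics and comfort.

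**3. Closed form.** Scale position from −0.5 to +0.5 over nine sockets. Its variance within a participant (divisor 8) is 0.1172. Shared drift adds c = 0.1172·D² to the covariance and to each variance. The spurious within-participant slope is c/(1.25 + c). The correlation is r = c/√[(1.25 + c)(1 + c)]. The test has 270 − 30 − 1 = 239 df, so its expected value is about r√239.

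| D | c | slope | r | r√239 | approx. false positives |
|---|---|---|---|---|---|
| 0.5 | 0.029 | 0.023 | 0.026 | 0.39 | 7% |
| 1 | 0.117 | 0.086 | 0.095 | 1.47 | 31% |
| 1.5 | 0.264 | 0.174 | 0.191 | 2.95 | 84% |

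**4. Simulation** (1000 runs per setting, regression of comfort on mechanics within participant, nominal 5%).

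| Assumed drift | No position or visit | With position | With position and visit |
|---|---|---|---|
| none | 5.0% | 4.9% | 5.3% |
| 1 SD, mechanics only | 4.6% | 5.4% | 5.8% |
| 1 SD, comfort only | 5.1% | 4.6% | 5.0% |
| 0.5 SD in both | 8.5% | 6.0% | 6.3% |
| 1 SD in both | 31.7% | 6.1% | 6.1% |
| 1 SD, opposite directions | 29.5% | 4.5% | 4.9% |
| 1.5 SD in both | 86.0% | 3.5% | 4.1% |
| visit shift 0.5 SD in both | 16.0% | 6.5% | 5.8% |
| visit shift 1 SD in both | 88.4% | 13.4% | 4.4% |

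The mean simulated slopes at D = 0.5, 1 and 1.5 were 0.023, 0.085 and 0.176, in line with step 3. A separate simulation with eight or nine sockets gave about 7%, 30% and 83–85% unadjusted, and 5–7% with a position term.

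**5. What the runs show.**
- Socket terms do not help: at 1 SD in both the rate is 35.8% with socket in the model.
- Position alone is not enough when the shift occurs between visits (13.4%).
- With one mean per participant the rate stays at about 4–6% in every setting.
- If drift differs between participants but averages zero (slope SD 1, independent in the two variables), the rate is 8.0% unadjusted and 7.5% with position. A common position term does not remove that smaller inflation.

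**The case against.** **Silence is not exclusion.** The article gives no complete covariate list for aim 1, the aim 2 list is openly illustrative, and a fuller protocol or analysis plan may name period and visit. This stands as a limit: the absence is shown only for the published text. What remains is that the article does choose adjusters by name, and every one is of a kind that cannot address this risk.

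**The unit of analysis is not stated.** The sample size rests on 30 observations, and with one row per participant the problem disappears. This also stands. Against it, the title promises within-subject effects, the design is a crossover, outcomes are averaged per intervention and ratings are made per socket. Collapsing to one row would discard the contrast the design was built for.

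**No drift is reported.** The earlier study found mechanics repeatable from trial to trial, beads are glued so as not to move, and donning variability in zero strain will be measured. The repeatability finding came from three steps per participant, so it does not bear on nine successive sockets or two visits. Still, nothing shows that drift occurs.

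**Nine rated rows may be too many.** Ratings are relative to the current socket, which suggests eight. With eight, the closed form gives 7%, 30% and 82%, so the conclusion is unchanged.

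**Stronger readings.** A reader might infer that session drift will produce false associations, or that every aim 2 correlation is affected. The documents support neither. The bias needs drift in both variables. Tissue stiffness is not described as repeated for each socket, so a correlation using it is not exposed in this way.

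**Conclusion.** The point holds conditionally. Randomising the order does not protect the aim 1 and 2 associations, and no named covariate would absorb a shared trend over test position or visit. If socket-level rows are analysed and both variables drift, the false-positive rate rises from 5% to about 7–9% at 0.5 SD, 30% at 1 SD and 85% at 1.5 SD. These drift sizes are assumptions, because the article gives none: the first is minor and the last serious. There is no inflation if only one variable drifts or if each participant contributes one row. In aim 2 the exposure is limited to clinical measures repeated per socket.

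This is an inexpensive improvement to the stated analysis, not evidence that its results will be wrong. It is worth making because significant terms pass directly into the predictive model and aim 3.

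**What to change.** In Statistical methods {20a}:
- State that the unit of analysis is socket within participant, with participant accounted for in the model.
- Include test position and visit as covariates in every aim 1 model.
- Include both as control variables in the aim 2 correlations whose clinical measure is repeated per socket (static radiographs, plantar pressure, gait). Correlations with measures taken once per participant, such as tissue stiffness, do not need them.

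Both terms are needed, since position alone left 13% false positives under a 1 SD visit shift.

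The cost is about two degrees of freedom, against 239 residual in the nine-socket layout. No new data are needed: Procedure for unblinding {17b} already refers to a list of each participant's sequence, and visit follows from the test date.

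Balanced (Williams) sequences would even out position and preceding socket, but they do not remove drift shared by two measured variables. They are optional and not the remedy here.

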**Fig. 10 Fig10:**
[figure not shown]
Biplane radiography data collection and processing. **A** Participants will walk on a treadmill while **B** synchronized biplane radiographs will be collected at 100 images per second (70 kV, 125 mA, 1 ms exposure per image). **C** CT scans of the residual femur will be collected and **D** used to create 3D bone models. **E** 3D bone pose will be determined using an automated volumetric model-based tracking process that matched digitally reconstructed radiographs to the original radiographs. **F** Six degree-of-freedom kinematics, including bone motion relative to the socket, will be calculated from late swing through push-off

##### Static radiographs

A series of three static radiographic images of the residual femur within each socket will be collected under increasing load applied to the prosthetic side (25%, 50%, 100% bodyweight), with the load measured by the force plate imbedded within the treadmill.

##### In-socket pressure

Pressure within the socket will be recorded at 65 Hz using 4 discrete pressure sensor pads, each less than 1 mm in thickness, each comprising 25 pressure sensors covering a 2 cm × 2 cm area (Pliance socket sensors, Novel Electronics, Inc.). The four pressure sensors will be placed in the anterior, posterior, medial, and lateral regions of the distal socket (Fig. 11).

**Fig. 11 Fig11:**
[figure not shown]
Reflective markers on a transfemoral amputee. Conventional motion capture will be used to measure overall body motion during gait

##### Plantar pressure

Foot plantar pressure will be measured at 100 Hz using insoles comprising 99 pressure sensors (Pedar system, Novel Electronics, Inc.) for the prosthetic and contralateral foot during each step of gait. At least 6 consecutive steps will be collected for each walking trial for each socket design.

##### Ground reaction forces

Ground reaction forces will be collected at 1000 Hz using a dual-belt instrumented treadmill (Bertec Corp). This system contains two side-by-side 30 × 180 cm belts. The belts are driven by independent (but synchronized) motor systems, and each belt/motor system is configured on a rigid platform supported by multi-axis load cells. This configuration enables the assessment of three-dimensional foot-ground reaction forces, applied torque, and center of pressure location independently for each foot. Ground reaction force data will be collected primarily to determine foot strike (greater than 50 N total force) and toe off (less than 50 N total force) during the gait cycle.

##### Motion capture

Conventional motion capture will record overall body motion (e.g., trunk lean, hip flexion/extension) during gait at 200 Hz using a set of 53 reflective markers placed on the participant (Fig. 10) (12 cameras, Vicon MX). Webcams placed behind and to the side of the participant will record standard video (30 Hz) of each walking trial.

##### Ultrasound elastography

Tissue stiffness in the anterior, posterior, medial, and lateral regions of the residual limb will be measured using ultrasound elastography [45]. Stiffness will be measured 7 cm proximal from the tip of the residual limb and separated into skin, fat, and muscle regions. Each measurement will comprise 4 regions of interest within each tissue and will be repeated three times. The average values of all measures will be used for analysis (Fig. 12).

**Fig. 12 Fig12:**
[figure not shown]
Ultrasound elastography performed on the residual limb of a transfemoral amputee (left). Tissue stiffness is color mapped onto the original ultrasound image and measured within 3 regions of interest (middle). Average values within each region are determined for each tissue (right)

##### Data processing and analysis

Residual femur bone tissue will be segmented from the CT images. All segmentation will be performed using the Mimics software (Materialise, Leuven, Belgium) using a combination of automated (thresholding and region growing) and manual segmentation strategies. We will measure the length of the residual femur and the bevel angle of the distal femur relative to the femur long axis.

##### Residual femur motion

Our validated volumetric model-based tracking system will match subject-specific 3D bone models to the biplane radiographs [42, 46] (Fig. 9). This tracking system has been validated in vivo to have an accuracy of 0.7 mm or better in translation and 0.9° or better in rotation [42] for 6 degree of freedom kinematics. Details describing the volumetric model-based tracking process, including hardware and software specifications, calibration and distortion correction procedures, and computational algorithms, have been described in detail [42, 47, 48]. The tracking process will yield the 3D motion of the residual femur during each walking trial. The dynamic 3D femur motion data will be smoothed using a fourth-order, low-pass Butterworth filter, with the filter frequency determined using residual analysis [49]. We will measure six degree of freedom motion of the femur relative to the socket (anterior-posterior, medial-lateral, and proximal-distal translation; anterior-posterior tilt, varus/valgus rotation, and internal/external rotation) and express our results as a percentage of the gait cycle. The analysis for aims 1 and 2 will focus on the medial-lateral and superior-inferior translation of the distal femur relative to the socket from late swing through midstance.

